## Abstract

**Background:**

Management of operating rooms is a critical point in health care organizations because surgical departments represent a significant cost in hospital budgets. Therefore, it is increasingly important that there is effective planning of elective, emergency, and day surgery and optimization of both the human and physical resources available, always maintaining a high level of care and health treatment. This would lead to a reduction in patient waiting lists and better performance not only of surgical departments but also of the entire hospital.

**Objective:**

This study aims to automatically collect data from a real surgical scenario to develop an integrated technological-organizational model that optimizes operating block resources.

**Methods:**

Each patient is tracked and located in real time by wearing a bracelet sensor with a unique identifier. Exploiting the indoor location, the software architecture is able to collect the time spent for every step inside the surgical block. This method does not in any way affect the level of assistance that the patient receives and always protects their privacy; in fact, after expressing informed consent, each patient will be associated with an anonymous identification number.

**Results:**

The preliminary results are promising, making the study feasible and functional. Times automatically recorded are much more precise than those collected by humans and reported in the organization’s information system. In addition, machine learning can exploit the historical data collection to predict the surgery time required for each patient according to the patient’s specific profile. Simulation can also be applied to reproduce the system’s functioning, evaluate current performance, and identify strategies to improve the efficiency of the operating block.

**Conclusions:**

This functional approach improves short- and long-term surgical planning, facilitating interaction between the various professionals involved in the operating block, optimizing the management of available resources, and guaranteeing a high level of patient care in an increasingly efficient health care system.

**Trial Registration:**

ClinicalTrials.gov NCT05106621; https://clinicaltrials.gov/ct2/show/NCT05106621

**International Registered Report Identifier (IRRID):**

DERR1-10.2196/45477

## Introduction

Operating rooms (ORs) are responsible for a large amount of profit and cost [1]. About 60% of all hospitalized patients are treated in the OR [2]. Surgical scheduling is a key process in perioperative organization; it begins by analyzing a list of daily cases and their expected duration. If cases consistently run longer, OR overuse will result in costly overtime pay and staff dissatisfaction. On the other hand, if actual case times are shorter than expected, OR underuse will lead to staff idle time, which is associated with up to 60% higher costs [3-5]. Also, decisions about the number of surgeries to perform during a typical day or week of activity in the OR have a considerable impact on downstream resources and on the efficient flow of patients in the system. Combining higher-level decisions, optimization logic, and management policies with an analysis of the consequences of these decisions that is enabled by simulation tools is an effective approach in health care [6-8]. Also, simulation is useful for testing the expected performance of a process, as well as its performance when it has been revised, modified, or optimized, before implementing it in practice and can also evaluate unexpected scenarios. Case duration prediction is usually demanded by the surgeon who reserves the time slot. With this method, it has been proven that surgeons underestimate case duration up to 42% of the time and overestimate it 32% of the time [9]. Another common approach is to use the electronic health record (EHR) to calculate case duration based on historical data for a given procedure. Decisions based on EHRs have a higher accuracy [10], but available EHRs only generate case durations for the average patient and do not take into account the patient’s specific profile (eg, their age, sex, BMI, allergies, or comorbidities). The rise of big data offers novel possibilities for patient-targeted predictions by exploiting machine learning (ML) and deep learning (DL) techniques. In particular, supervised learning techniques are able to identify latent patterns among large quantities of data by training the model to minimize a loss function between the actual output and the desired (ie, supervised) one. The model is afterward able to generalize on unseen cases that belong to the same data distribution. For this reason, ML is also gathering attention in the medical field for both clinical and organizational purposes. Notwithstanding this, we are still in the early phase, and there are several challenges to deal with [11-14] .The main issue to exploit ML is providing accurate and noise-absent samples to the model, which is critical when historical data are collected by human processes. In light of this, the aim of our research project is to develop an integrated technological-organizational model capable of exploiting data derived from ORs to optimize the management and organization of the whole operating block. To achieve such a result, we have first developed an internet of things (IoT) architecture that is able to collect real data to minimize the presence of errors or noise in data and maximize ML performance. Next, we will proceed to develop an optimal scheduler for surgical procedures supported by simulation and able to integrate clinical and anamnestic information with data derived from an analysis of surgical timing and time spent in the recovery room (RR) so as to optimize the system’s organization [15].

## Methods

### Overview

Our research work is a prospective, single-center, interventional study. Patients are included if they are older that the age of majority (18 years in the country where the protocol was drafted); provide signed informed consent; and are undergoing elective abdominal, thoracic, vascular, gynecological, or plastic surgery. If the patient agrees to participate in the study, data will be collected on the expected and actual time from the patient’s entry to the operating compartment to their exit. In particular, time spent in the operating room, surgical time, and length of stay in the operating room will be recorded. This information will be integrated with anamnestic data and data relating to hospital stay [16-18]. The goal is to create a technological-organizational programming model able to optimize operating block management. In this work, we identified 50 simple variables for each patient. These features will form a single data set instance. We decided to focus our attention on ML methods instead of traditional methods, as the latter may not be sufficient for this task, often requiring assumptions about data distribution, and may not be able to handle the complexity and volume of the data that we want to use to make predictions. On the other hand, ML methodologies can capture nonlinear relationships between variables, which can be important for predicting times accurately. Moreover, ML algorithms can benefit from large amounts of data to identify patterns, and EHR data contains a large number of variables, including patient anamnestic data, medical records, and surgical details. ML algorithms can extract knowledge from this data and use it for making a much better and more accurate prediction. Finally, ML methods can handle outliers, which can be common in EHR data, and ML methods can generalize well to new data. This is important because we can make predictions for surgery time for patients who are not in the original data set. In this study, we will collect data from 1200 patients. Bearing in mind that this data set will have to provide data to both create the model and validate it, the data set will be divided into 3 parts: a training set (60%), a validation set (20%), and a test set (20%). The project is divided into three phases: (1) using the IoT for data collection and patient enrollment, (2) machine learning for time prediction, and (3) optimization with discrete-events simulation.

In the first phase, which forms the focus of this paper, we developed an IoT architecture to perform indoor localization of patients in ORs and in RRs. Patients who decide to participate in the study are asked to give informed consent. If they agree, they are provided with a personal Bluetooth Low Energy (BLE) beacon tag when entering the operating block or in the ward. The tags are detected by detectors (Raspberry Pi devices; Raspberry Pi Ltd) that are located in the environment of interest. The detectors communicate with a private local area network (LAN) to manage data flow and to provide additional security levels. Moreover, the LAN does not have any internet access, so the network is not vulnerable to any external attacks. The access to the server, to the sensor configuration module, and to the association interface is password protected and all communication to the server is encrypted. In this section, we describe the components and our solution for monitoring patients’ movements inside the surgical block. We realized a client-server architecture that provides communication between the sensor modules and the server in our system. The whole IoT system has several parts, which are listed below.

### BLE Beacons

BLE is a wireless communication technology designed for low-power devices that require short-range connectivity and is widely used in IoT environments [19]. BLE technology operates on 2 main channels: advertising and data. For our purposes, we decided to use only the advertising channel in order to detect beacons when they are near to our sensors. For this reason, we adopted the iBeacon protocol (Apple Inc). The iBeacon protocol identifies beacons with a triplet of universally unique identifiers (UUIDs). For this prototype we used the BlueUp (BlueUp Srl) beacon, which has 800 milliseconds of advertisement time. Each patient will be associated with a beacon connected to a numerical, progressive, and anonymous ID to respect patient privacy. The beacon is assigned to each patient and is worn as a bracelet with a wrist band. Being affixed to the patient’s wrist is the best compromise between comfort and signal efficiency.

### Sensor Modules

As a sensor module, we used a Raspberry Pi 4 device running the 64-bit Raspian OS. The sensor module continually scans for BLE advertisements, checking them against a list of preregistered beacons provided by the central server. Using a list allows us to ignore nonregistered beacons, saving bandwidth and processing resources. The sensors autoconfigure themselves. They can be rebooted or shut down at any time. When the sensors receive a beacon advertisement, they append the package received and its timestamp into a JSON file and forward the information to the central server over a transmission control protocol.

We estimate the patient’s presence inside a specific room in the operating block using the residence time within the range of action of the sensor. Every sensor has its own residence time and a tunable threshold of signal sensitivity. This last parameter can increase or decrease the sensor’s range of action. If the beacon remains for a certain amount of time in the action range of a sensor, the beacon is marked as entered into the room.

### Central Server

The central server indexes and collects the data coming from the sensor modules. It has the following duties: (1) storing records coming from each detector in a MongoDB database (MongoDB Inc); (2) coordinating distributed solution and message exchange using a publish-subscribe mechanism based on message queue telemetry transport (MQTT), and finally, (3) exposing a web server that is used as a unique interface between the software architecture and the hospital medical staff. The central server hosts the eclipse Mosquitto-based MQTT broker (Eclipse Foundation Inc). When it receives the packets from the sensors, it determines whether the beacon is in the room where the sensor is located. Our implementation of the beacon server used a Python-based service and exploited the MongoDB database to store the various events. The data format is shown in Table 1. The central server also has the duty to send information to the edge modules regarding the list of preregistered beacons, the identity of the sensor itself, and a time-synchronization message.

**Table 1 table1:** Data stored by the server for each sensor when an entry is recorded in the database.

Fields	Description
uuid	Universally unique identifier for the beacon
minor	Contains the unique beacon ID
macAddress	Beacon MAC address
timestamp	First detection timestamp
last_detection	Last detection timestamp (continuously updated)
flag	Boolean value that if true specifies that the patient is currently in that specific room
Patient ID	Unique number assigned to a specific patient

### Client Interface

The client interface, hosted by the central server, offers several functionalities. The first is enrollment. Patient enrollment is done by a member of the medical staff when the patient enters the operating block to undergo surgery. The enrollment is performed using a tablet device that communicates with the web application and by providing the necessary information. The system also provides a graphical interface able to monitor in real time the various movements of patients (Figures 1 and 2).

**Figure 1 figure1:**
[figure not shown]
Screenshot of the home page of the web application responsible for the beacon-patient association. (In the web application, the term “bangle” is used to describe the beacon.).

**Figure 2 figure2:**
[figure not shown]
Screenshot of the graphical interface for monitoring patient movements inside the operating block. Green cells indicate that the patient is near the sensor that is associated with that specific room or place. Red cells indicate that no tracking device has been detected for some time. Finally, gray cells indicate that there is no tracking data for that place.

### Ethics Approval

The study was approved by the Comitato Etico Unico per l’Area Vasta Emilia Nord, a local ethics committee (1284/2020/OSS/AOUPR), and was registered on ClinicalTrials.gov on January 11, 2021 (NCT05106621). Written informed consent was obtained for all study participants. The participation of individuals of legal age capable of giving informed consent as subjects in medical research must be voluntary (World Medical Association Helsinki Declaration). The data are collected anonymously and with respect for the privacy of patients.

## Results

This research was financially supported by the FIL-Quota Incentivante program of the University of Parma and cosponsored by Fondazione Cariparma with approval in the second half of 2019. As of February 2023, approximately 1000 patients have been enrolled, with an enrollment target of not less than 1200 to 1300.

We schematized a generic path a patient could follow inside the operating block (Figures 3-6).

In addition, if a patient agrees to participate in the study, we collect the following: data about the surgical procedure, personal and anamnestic data, data from the RR, and data on the hospital stay, such as whether the patient was admitted to the intensive care unit.

The prototype of the IoT architecture described and illustrated above was installed successfully in the surgical block and is still functional. We collected data from more than 100 patients. It is possible to see in the final output illustration (Table 2) that combining the data from various sensors allowed us to reconstruct the patient’s path.

The second step will involve the application of ML and DL algorithms to study the feasibility of predicting surgical procedure time by providing features of the patient and of the surgery as input. Because of the lack of public data sets or similar approaches in the scientific literature, we are currently performing a feature selection task among more than 50 variables to identify which features can maximize prediction accuracy in terms of the root mean squared error of surgery time. Several ML approaches are possible since the task of intraoperative time prediction can be modeled in different ways. Since the total time in the operating block is the sum of the time spent in the OR and in the RR, this prediction task can be modeled using 2 different ML models or a unique one that tries to directly estimate the total time. Moreover, depending on the data set size, tree-based ensemble models (eg, gradient boosting or extreme gradient boosting; XGBoost) could better suit the task. On the other hand, the complexity of the task and the nonlinear dependency of several features within the target variable of “time required” may require the use of deep neural networks. DL requires larger data collection, but at the same time, it would be possible to exploit its ability to perform representation learning of the input, requiring less feature engineering.

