**Figure 3 figure3:**
[figure not shown]
Generic patient path illustration within the operating block. The patient accesses the operating block at tracking point 1. Then, the patient’s stretcher is swapped at point 2, and a member of medical staff assigns them a beacon and sets up the associated ID. Next, the patient goes to the assigned operating room (point 3). Once the surgical procedure ends, the patient is transferred to the recovery room (point 5), where they are monitored after the procedure. The patient can then either exit the operating block from point 6 or can return to the operating room if there are acute surgical complications. Moreover, during these activities, the patient can remain idle at an unspecified point in the corridor, represented by point 4. Personal data are extracted from the information systems of the Ospedale Maggiore of Parma using pseudoanonymization techniques.

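### Total operating-block time is equated with OR plus RR time, but the article's own patient path and entry-to-exit interval include time outside both rooms, so a summed two-model prediction would be too short on average

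*Protocol article*

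**What the plan says.** In the protocol article, the Results section describes the second step, machine-learning prediction of times. It gives as a premise "Since the total time in the operating block is the sum of the time spent in the OR and in the RR" and concludes that "this prediction task can be modeled using 2 different ML models or a unique one that tries to directly estimate the total time". The choice between the two is left open. The accuracy criterion named for feature selection in the same paragraph is the root mean squared error of surgery time.

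Two other places describe the same block differently:

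- **Methods, Overview:** "data will be collected on the expected and actual time from the patient’s entry to the operating compartment to their exit". The sentence after it gives particulars: "time spent in the operating room, surgical time, and length of stay in the operating room will be recorded".
- **Figure 3, legend:** "The patient accesses the operating block at tracking point 1". The "stretcher is swapped at point 2, and a member of medical staff assigns them a beacon and sets up the associated ID". The OR is point 3, the RR is point 5 and the exit is point 6. In addition, "during these activities, the patient can remain idle at an unspecified point in the corridor, represented by point 4".

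**The concern.** The identity in Results has two components, while the path in Figure 3 has more than two places where time can pass. Access, stretcher swap, corridor waiting and transfers lie inside the block and in neither room. An interval that runs from entry to exit contains all of them.

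This matters because the identity is the stated reason for treating the sum of two models and one direct model as two ways to do one task. If the direct model is trained on observed entry-to-exit time, the two options estimate different quantities. The sum leaves out a component that cannot be negative. More patients or a better algorithm will not remove that error, because it comes from the definition of the target. If each option were then scored against its own target, the comparison would not be like for like.

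What is at stake is the prediction of total block time and any later use of it. The Discussion says that the simulation and scheduling logic are to be improved with the model's predictions. Waiting and transfer time is also part of the patient flow that the tracking system was built to record.

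**Working it through.** The article gives no figure to reproduce here. The check is an accounting identity, followed by an illustration under assumed durations.

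**1. The identity.** Let O be OR time, R be RR time, and W ≥ 0 be the time at points 1, 2, 4 and 6 and in transfer.

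- Results: T = O + R.
- Methods Overview with the Figure 3 legend: T = exit − entry = O + R + W.

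The two agree only if W = 0. The stretcher swap belongs to the generic path, so W is above zero in the ordinary case. Corridor idling is described as possible, not universal. Nothing in the text assigns swap or corridor time to the OR or the RR, and the corridor has its own point.

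**2. Bias of the sum.** Suppose both component models are unbiased. The error of the summed prediction against T then has mean E(Ô + R̂ − T) = −E(W). The mean shortfall equals the mean non-room time.

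**3. Individual predictions.** For a patient with non-room time w and a normal prediction error with SD s, P(prediction too short) = Φ(w/s). The values of w and s are assumptions, in minutes.

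| w | s | Φ(w/s) | RMSE = √(s² + w²) |
|---|---|---|---|
| 5 | 50 | 0.540 | 50.2 |
| 10 | 30 | 0.631 | 31.6 |
| 30 | 15 | 0.977 | 33.5 |

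With w = 10 and s = 30, 63% of predictions are too short and 37% too long. The shortfall is a property of the mean, not of each patient.

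**4. Size of the avoidable error.** Assume error SDs of 40 min (OR) and 30 min (RR), independent of each other and of W. Scored against O + R, the RMSE is √(40² + 30²) = 50.0 min. Scored against T, the sum has RMSE √(2500 + SD(W)² + E(W)²). A third component that supplies only the mean of W leaves √(2500 + SD(W)²).

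| Assumed mean/SD of W | Sum of two models | With mean of W added | Avoidable excess |
|---|---|---|---|
| 10/8 | √2664 = 51.6 | √2564 = 50.6 | 2% |
| 25/20 | √3525 = 59.4 | √2900 = 53.9 | 10% |
| 40/30 | √5000 = 70.7 | √3400 = 58.3 | 21% |

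Against 50.0 the first column is 3%, 19% and 41% higher. Part of that is variation in W, which remains unless W can be predicted, so the last column is the fair measure of what the definition costs.

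**5. Unequal targets.** On the same assumptions, a direct model of T that captures only the mean of W has RMSE 50.6, 53.9 or 58.3. The two-model option scored against O + R shows 50.0. It would look better only because it omits W.

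**The case against.** The strongest reply is that little in the article depends on the identity. The stated aim of the second step is surgical procedure time, and the named criterion is the error of surgery time, which contains no corridor or swap time. The two-model route is one of two open options, and a direct model trained on observed entry-to-exit time would include the missing part. The article says that its focus is the first phase, data collection, and no rule for scoring the options is given. The simulation is described as reproducing patient flow and is not said to take OR plus RR as block time. All of this stands. It confines the problem to total block time and makes the unequal comparison a risk rather than a stated plan.

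Rooms are assigned by sensor range and residence time (Sensor Modules), so some corridor time near a room might be logged as room time. The article does not say so, and this would not cover the swap at point 2.

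A reader might infer that every patient who waits gets a prediction that is too short. That does not follow: O + R is below entry-to-exit time for each such patient, but prediction errors go both ways.

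A reader might also infer from the list in the Methods Overview, which names OR time twice and omits the RR, that RR or total time goes unrecorded. The documents do not support this. The sentence just before the list covers entry to exit, and RR data are named in the Introduction and in Results. The duplicate is a wording slip.

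**Conclusion.** The point holds in a limited form. The identity in Results contradicts the path in Figure 3 and the interval in the Methods Overview. If total block time is predicted by adding an OR model and an RR model, it will be underestimated on average by the mean non-room time, and its target will differ from that of a direct entry-to-exit model. This assumes that the component models are unbiased for OR and RR time and that non-room time is not absorbed into the room records.

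The size is not known. The text gives no durations for the points outside the rooms; the contents of Figure 4 and of the Table 2 cited in Results, which may bear on this, were not in the text available for this check. The minutes and percentages above only illustrate. The surgery-time criterion is unaffected. The definition should be corrected before total block time is modelled, because it builds in a systematic error that is cheap to remove.

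**What to change.** Choose one of two definitions and use it throughout.

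1. **Entry-to-exit time.** Define total block time as exit minus a stated start point. Derive the non-room remainder as that total minus OR time minus RR time, with each room summed over all visits because Figure 3 allows a return to the OR. Model the remainder as a third component, and score the one-model and two-model options against the same observed total.
2. **Room occupancy.** State the target as OR plus RR occupancy, do not call it total block time, and train and score both options on that quantity.

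Under the first definition the start point needs care. Figure 3 has the beacon assigned at point 2, after access at point 1, while the Methods Overview allows it at block entry or in the ward. For patients tagged at point 2, beacon records cannot give the true entry time. The start should therefore be a point observed for everyone, or the entry time should come from another named source.

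As a minor wording correction, replace the second OR item in the Methods Overview list with RR time.

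The cost is a sentence or two, one derived variable, and a somewhat less favourable reported error for the two-model option.
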